**Results:**

Fourteen districts were selected by the Ministry of Health in September 2025 for VectorCam introduction. A pilot phase conducted between December 2025 and January 2026 in two districts was used to refine implementation strategies and research tools through stakeholder workshops. Ethical approval was obtained from Johns Hopkins in January 2026 and Ugandan ethics committees in September 2025. Implementation began in February 2026 and will continue through March 2027 with concurrent data collection and analysis throughout the implementation timeline.

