## Methods

### Study Design Overview

This study uses a mixed methods, hybrid type III implementation-effectiveness design [33]. The primary aim is to evaluate implementation outcomes, including acceptability, feasibility, fidelity, and cost, while the secondary aim is to assess preliminary effectiveness outcomes, including technical accuracy of mosquito identification and operational use of VectorCam data in decision-making. Table 1 outlines these outcomes along with assessment methodology for each, demonstrating our multiple methods of data collection that will generate predefined key measures and are analyzed using both qualitative and quantitative approaches.

**Table 1 table1:** Implementation and effectiveness outcomes, methods, and metrics by aim.

Outcome	Methods of data collection	Key measures	Planned analysis
Aim 1: assessment of contextual determinants	CFIR^a^-determinants evaluation survey with implementers; ERIC^b^ strategy matching tool Semistructured pre- and post-KIIs^c^ evaluating context with users^d^	CFIR barriers and facilitators by domain	Descriptive summaries of survey notes; quantitative summaries of Likert Scale ratings Thematic analysis of CFIR constructs; cross-district & cross-wave comparison matrices
Aim 2: acceptability, feasibility, fidelity (qualitative)	Semistructured pre- and post-KIIs evaluating implementation with users^d^ Midpoint IDIs^e^ with Master Trainers, VCOs^f^, and VHTs^g^ Quarterly stakeholder engagement meeting FRAME-IS^h^ documentation tool	Perceived usefulness, ease of use, workflow fit, perceived protocol adherence, sustained use, pain points, adaptation tracking	Thematic analysis; descriptive statistics; longitudinal summaries by district and rollout wave
Aim 2: fidelity (quantitative)	App usage and completeness metrics Field observation checklist and supervisory toolkit	Completeness of reporting; protocol adherence, district-level sustained use Protocol adherence rate	Proportions with 95% CIs; ordinal or binary mixed models where appropriate; district quarter trend plots
Aim 2: cost	Costing database, budgets, procurement and supervision records	Total and unit costs, budget impact, scale-up costs	Budget impact analysis modeling for 1-year, 3-year, and 5-year scenarios; ingredients-based costing; annualization of capital costs; one-way sensitivity analysis

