The remaining 12 districts will implement the package in 4 sequential rollout phases, with 3 districts added every 3 months following completion of the pilot phase. This design enables evaluation of implementation processes across diverse contexts and over time, while allowing for iterative refinement of strategies between phases. Districts are assigned to rollout waves using restricted randomization at the district level via a computer-generated random sequence created by a study programmer prior to implementation. To ensure geographic balance, the allocation sequence will be constrained such that no rollout group includes more than one district from the same region. This approach was developed collaboratively by the study team and Uganda’s MOH to support evaluation across different districts while promoting equitable distribution of the intervention across regions during rollout. The rollout waves are intended to support implementation sequencing and adaptive learning rather than serve as comparison groups for causal inference. Multimedia Appendices 4 and 5 show information on the districts in each rollout group. To facilitate interpretation of our outcomes, contextual district characteristics, including malaria burden and workforce composition (eg number of VHTs and VCOs per district), will be documented during implementation activities and added descriptively to the table shown in Multimedia Appendix 5.

Key participants include VHTs, VCOs, master trainers (ie, district-level supervisors who are trained in the VectorCam system), District Health Officers, and staff from the National Malaria Elimination Division (NMED), representing multiple levels of the health system engaged in malaria surveillance and control.

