Next, we will explore VectorCam’s operational effectiveness and data use on malaria control decision-making by interviewing 8-10 MOH-NMED staff and District Health Officers. An interview guide was developed to facilitate the KIIs with national and district-level decision makers to collect qualitative information regarding operational effectiveness and VectorCam data use. The NMED groups that will be interviewed will either have routine interactions with the entomology database, responsibilities for improving the database, and/or responsibilities that involve using the database to make decisions about malaria control programs, including roles such as the Director of the National Malaria Program, Information Technology Senior Developer, lead entomologists, and coordinators of routine surveillance activities. Interviews will explore perceptions of the reliability and utility of VectorCam data, comparisons to previous surveillance approaches, and examples of how data informed vector control interventions or planning. Interviews will be conducted a minimum of 6 months after implementation in each district cohort to allow sufficient time for data review and use.

Lastly, a researcher from either Makerere University or Johns Hopkins University will attend NMED’s quarterly meetings and use the NMED quarterly meeting attendance and observational checklist to document how the VectorCam data are reviewed and used during routine decision-making processes. The checklist will capture whether VectorCam data were presented, discussed, or referenced in relation to surveillance planning, vector control activities, resource prioritization, or other operational decisions. Findings from these observations will be triangulated with key informant interviews to assess the perceived utility and operational use of VectorCam data.

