## Results

In collaboration with Uganda’s Ministry of Health, the study team identified 22 districts that met the inclusion criteria, from which 14 districts were selected to receive the VectorCam intervention in September 2025. The pilot phase was conducted from December 2025 to January 2026, during which research tools were tested during rollout in two districts. Stakeholder workshops in the pilot phase were used to refine the implementation package and research instruments. Ethics approval was granted in January 2026. Data collection for the first rollout group began in February 2026, initiating a year-long data collection period. As of March 2026, the second rollout group of 3 districts is scheduled to begin data collection in June 2026. Data collection and subsequent analysis will be concurrent in districts where the intervention has been deployed and are expected to continue through March 2027.

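### The 6-month minimum before decision-maker interviews cannot be met for wave 4 within a data-collection period that ends in March 2027

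*Protocol article*

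**What the plan says.** **The interview rule.** The Aim 3 section plans 8-10 interviews with national malaria programme staff and District Health Officers on how VectorCam data are used. On timing it says: "Interviews will be conducted a minimum of 6 months after implementation in each district cohort". The reason given is that data need time to be reviewed and used.

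**The rollout.** Study Setting and Participants says: "The remaining 12 districts will implement the package in 4 sequential rollout phases". It gives the spacing of these phases as follows: "with 3 districts added every 3 months following completion of the pilot phase".

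**The dates.** The main Results section says: "Data collection for the first rollout group began in February 2026, initiating a year-long data collection period". It adds that "the second rollout group of 3 districts is scheduled to begin data collection in June 2026", and that collection and analysis "are expected to continue through March 2027". The Results paragraph of the Abstract has the same end date: "Implementation began in February 2026 and will continue through March 2027".

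**The analysis.** For operational effectiveness and data use, Table 1 plans a descriptive comparison of data-use indicators across districts and rollout phases. It lists the quarterly national meeting checklist alongside the decision-maker interviews as a data source.

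No section shown exempts the last wave from the 6-month minimum or extends collection for it.

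**The concern.** The waiting rule applies to every district cohort, but the last cohort enters less than 6 months before collection is due to stop. Staff would have to leave wave 4 out of the interviews, interview about it before the time the plan itself considers sufficient, or run past the stated end. The protocol does not say which, so the choice would be made ad hoc late in the study.

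The wave matters because the package is refined between phases. Wave 4 receives the version with the most adaptation behind it, which is of particular interest for scale-up. An undeclared gap there would also leave the cross-phase comparison in Table 1 without compliant interview evidence for its last phase.

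**Working it through.** **Inputs**
- Wave 1 start: February 2026 (main Results).
- Wave 2 start: June 2026 (main Results). This is 4 months after wave 1, not 3.
- Spacing: 3 months; four waves of 3 districts (Study Setting and Participants).
- Minimum lag for decision-maker interviews: 6 months (Aim 3).
- Lag for user post-implementation interviews: 3 months (Aim 1).
- End: March 2027 (main Results and Abstract), taken as 31 March 2027. Results also calls the collection period year-long. The March date is later and so more favourable to the plan.

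The start months of waves 3 and 4 are not in the text shown; they are inferred from the 3-month spacing.

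**Reproducing the plan's end date.** With wave 2 in June 2026, wave 4 starts two steps later: June + 2 × 3 months = December 2026. Adding the 3-month user follow-up gives December 2026 + 3 months = March 2027, which is the stated end. The calendar is thus consistent with the 3-month user interviews, but not with the 6-month rule.

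**Latest admissible start.** 31 March 2027 − 6 months = 30 September 2026.

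**Eligibility month = wave start + 6 months**

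| Wave | Start, 3-month steps from February | Eligible | Start, June for wave 2 then 3-month steps | Eligible |
|---|---|---|---|---|
| 1 | Feb 2026 | Aug 2026 | Feb 2026 | Aug 2026 |
| 2 | May 2026 | Nov 2026 | Jun 2026 | Dec 2026 |
| 3 | Aug 2026 | Feb 2027 | Sep 2026 | Mar 2027 |
| 4 | Nov 2026 | **May 2027** | Dec 2026 | **Jun 2027** |

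Wave 4 misses the end date on both schedules, by two calendar months (March to May) or three (March to June). The result does not depend on the day of the month. By 31 March 2027, wave 4 has 4.0 to 4.9 months of follow-up if it starts in November and 3.0 to 3.9 months if it starts in December.

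Wave 3 meets the rule on both schedules. On the June-based one, its eligibility falls in the final month, with a latest date of 30 March 2027 if it starts on 30 September.

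**Share affected.** 3 / 12 = 25% of districts.

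**The case against.** The strongest reply is that little is lost. Only the decision-maker interviews carry the 6-month wait. The national quarterly meeting checklist has none and can record use of wave 4 data, and the app logs and 3-month user interviews also reach wave 4. The 8-10 interviews are shared between national staff and District Health Officers and aim at thematic saturation, so they would not cover 12 districts one by one on any calendar. Effectiveness is the secondary aim, and Challenges and Limitations calls its outcomes preliminary and descriptive. All of this stands, and it limits the consequence. It does not make the rule workable: the minimum is set for each cohort, and the checklist is to be triangulated with these interviews, not to replace them.

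A second reply is that the wave-by-wave timeline is in Multimedia Appendix 3, which is not shown, and that March 2027 is only an expected end. This is fair as to exact months. But to satisfy the rule by March 2027, an appendix would have to start wave 4 by the end of September 2026, against the spacing given in the text.

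Three stronger readings are tempting, and the documents do not support them.
- A reader might infer that the whole data-use outcome is missing for a quarter of districts. The checklist rules that out.
- A reader might infer that wave 3 is lost too, making half the districts. That needs a further slip that no section states; on the dates in the text, wave 3 fits.
- A reader might infer that wave summaries of sustained use are invalid because log lengths differ. Unequal follow-up is inherent in a staggered rollout. The plan summarizes these data descriptively with district-quarter trend plots, and says the waves are not comparison groups for causal inference.

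**Conclusion.** The point holds in a limited form: a procedure fixed in the protocol cannot be carried out as written for wave 4, which is 3 of 12 districts. The earliest compliant interview falls in May or June 2027, against an expected end in March 2027. Wave 3 is feasible, but has no slack on the June-based schedule.

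What is at stake is compliant interview evidence about wave 4 and its place in the cross-phase comparison. No primary implementation outcome, estimate or sample size is affected. The conclusion assumes 3-month spacing for the undated waves and an end no later than 31 March 2027. Severity: should be fixed.

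**What to change.** Reconcile the interview timing in Aim 3 with the rollout spacing in Study Setting and Participants and with the dates in the Abstract and main Results, by one of two routes.

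(a) Keep the 6-month minimum for every cohort and extend only the decision-maker interviews to about June 2027. The cost is up to three more months for a few of the 8-10 interviews; nothing else need be prolonged.

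(b) Keep March 2027 and state that the 6-month interviews cover only cohorts that have reached 6 months by then: waves 1 and 2, and wave 3 if it starts on time. Limit the interview-based conclusions on data use, and the interview part of the cross-phase comparison in Table 1, to those cohorts, and say that the checklist is the source for wave 4. The cost is wording and a narrower stated scope.

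On the stated schedule wave 4 has yet to start, so either choice can be recorded prospectively.

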Aim 3: technical effectiveness	Validation subset with VectorCam, routine method, and PCR^i^ (or equivalent)	Sensitivity, specificity, PPV^j^, NPV^k^, F1-score, agreement	Diagnostic accuracy analysis with 95% CIs; paired comparison when both methods are available; descriptive comparison of classification performance
Aim 3: operational effectiveness and data use	Quarterly NMED^l^ meeting attendance checklist KIIs to measure time allocation with users KIIs with district and national decision-makers	Use of data in planning; reporting timeliness Time allocation; task-shifting model metrics Data usage by decision-makers; impact on malaria control actions	Descriptive comparisons of time allocation metrics and data-use indicators across districts and rollout phases; mixed effects regression for time metrics; qualitative thematic analysis of data-use pathways

^a^CFIR: Consolidated Framework for Implementation Research.

^b^ERIC: Expert Recommendations for Implementing Change.

^c^KII: key informant interview.

^d^Pre and postinterviews are conducted 1-week after training and 3 months after implementation.

^e^IDI: in-depth interview.

^f^VCO: vector control officer.

^g^VHT: village health team.

^h^FRAME-IS: Framework for Reporting Adaptations and Modifications–Enhanced for Implementation Strategies.

^i^PCR: polymerase chain reaction.

^j^PPV: positive predictive value.

^k^NPV: negative predictive value.

^l^NMED: National Malaria Elimination Division.

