### Intervention Description

The proposed task-shifting model for vector surveillance includes the VectorCam hardware and software (intervention) along with the strategies supporting its integration into Uganda’s routine vector surveillance program (implementation package). We used a human-centered design approach to developing the implementation package, with a particular focus on determining the details of the implementation strategies and materials. The implementation package was co-designed in consultation with national, district, and community-level stakeholders during a collaborative workshop held in August 2025. The participants included officials from the Ministry of Health, master (lead) VCOs, district VCOs, and members of the research team.

The intervention includes VectorCam imaging devices, smartphones preloaded with the VectorCam application, and charging accessories provided to each district and shown in Multimedia Appendix 6. The package includes 4 core implementation strategies: (1) a training toolkit and capacity building, (2) data-based decision making, (3) a supervisory toolkit and quality assurance, and (4) learning loops and procedures for ongoing technical support. These strategies are designed to address known barriers to implementation by improving user knowledge and skills, strengthening feedback and accountability systems, reinforcing perceived usefulness, and supporting integration into routine workflows. Because VectorCam is designed to support task shifting of surveillance activities to community-level personnel, the study will also evaluate the training intensity qualitatively and by number of retraining sessions completed, supervision requirements, technical support needs, and workflow adaptations necessary to maintain high-quality surveillance data. Figure 1 depicts the implementation package components conceptually.

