### Aim 3: Evaluation of Effectiveness

Effectiveness of the VectorCam intervention (as delivered with implementation strategies) in maintaining accuracy, improving time allocation metrics, and supporting operational use of surveillance data will be assessed with a combination of KIIs, quantitative analyses of system data logs, and qualitative interviews with national and district-level decision-makers. This aim is designed to generate preliminary evidence regarding VectorCam’s performance under ideal implementation conditions and whether the task-shifting model is associated with improvements in data quality and timelier, evidence-based decision-making relative to microscopy-based surveillance. Routine microscope-based entomological surveillance conducted by district entomology teams serves as the comparator condition, as it represents the standard of practice within Uganda’s national malaria surveillance system.

Methods of data collection for Aim 3 include:

Pre- and post-KIIs to evaluate time allocation with usersApp-recorded data logging time spent per mosquito identification eventMolecular analysis comparisonKIIs with national and district-level decision-makers on operational effectiveness and data useNMED quarterly meeting attendance and observational checklist

Pre- and postimplementation interviews with VHTs and VCOs will be used to assess the time required for mosquito identification and data submission. This tool is designed to be utilized at the same time point as the pre- and post-KIIs for data collection within Aims 1 and 2. Participants will be asked to describe the average time spent on identification tasks before and after the introduction of VectorCam, including steps related to specimen preparation, processing, and reporting. Questions on the KII guides differ for VHTs and VCOs in order to capture changes to workflow based on the task-shifting model.

Quantitative data on actual time spent per mosquito identification event will be extracted from VectorCam usage logs over the study period. Logs will include timestamps marking initiation of identification, confirmation of results, and data upload.

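### The NMED meeting checklist is described as recording use of VectorCam data only, so the observed data-use outcome has no value for the microscopy comparator that Aim 3 names

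*Protocol article*

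**What the plan says.** In the protocol article, the section on Aim 3 (Evaluation of Effectiveness) sets a comparative question. The study is to give preliminary evidence on whether the model is associated with "improvements in data quality and timelier, evidence-based decision-making relative to microscopy-based surveillance". The comparator is named: "Routine microscope-based entomological surveillance conducted by district entomology teams serves as the comparator condition". The section on Sample Size and Power, while stating that no formal power calculation was done, expects the sample to be enough to detect meaningful differences in data usage, among other outcomes.

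Data use is observed directly with one tool. A researcher attends NMED's quarterly meetings with an "observational checklist to document how the VectorCam data are reviewed and used during routine decision-making processes". Its content is described as follows: "The checklist will capture whether VectorCam data were presented, discussed, or referenced in relation to surveillance planning"; the sentence goes on to list vector control, priorities for resources and other operational decisions. Table 1 gives the planned analysis: "Descriptive comparisons of time allocation metrics and data-use indicators across districts and rollout phases".

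The second source on data use is a set of 8-10 interviews with national and district decision-makers, held at least 6 months after implementation. They cover, among other things, how VectorCam compares with earlier surveillance approaches. The section on Challenges and Limitations says that no meaningful concurrent or historical control could be built, and that effectiveness results are to be read as preliminary and descriptive.

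**The concern.** The question concerns decision-making under VectorCam compared with decision-making under microscopy. The tool that observes decision-making is described as scoring VectorCam data only. An indicator defined for one condition cannot be compared with the other, even descriptively. If routine microscopy data are discussed at the same meeting, the form as described leaves no trace of it.

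The planned axis of comparison adds a second difficulty. Across rollout phases the number of districts able to supply VectorCam data grows by design. A higher score at later meetings could mean that NMED makes more use of the data it receives, or only that more districts send such data. The checklist as described cannot tell these apart.

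At stake is the conclusion on data use, which is meant to inform national scale-up. Checklist results triangulated with favourable interviews could be read as showing a gain over microscopy that was not observed on both sides.

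**Working it through.** No sample size, power or precision figure underlies this point. The check sets the stated comparison against what each tool records, then tabulates the rollout.

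**Step 1. Does each data-use source cover the comparator?**

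| Source | Records VectorCam data use | Records microscopy data use | Timing |
|---|---|---|---|
| NMED meeting checklist (Aim 3) | Yes: presented, discussed or referenced | No item described | Quarterly; no observation before VectorCam described |
| Decision-maker interviews, 8-10 people (Aim 3) | Yes, as perceived | Only by recall of earlier approaches | After implementation only, at least 6 months on |

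The one prospective, directly observed source has an empty comparator column. The other fills it by recall, with no baseline interview described.

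**Step 2. How does availability change over the planned comparison?** Inputs from Study Setting and Participants: 12 districts, 3 added every 3 months. Districts live in quarter q = 3 × q; districts not yet live = 12 − 3 × q.

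| Quarter | Live with VectorCam | Not yet rolled out |
|---|---|---|
| 1 | 3 | 9 |
| 2 | 6 | 6 |
| 3 | 9 | 3 |
| 4 | 12 | 0 |

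If the two pilot districts go on reporting (an assumption), the live series is 5, 8, 11, 14. The calendar is nominal: Results gives February 2026 for the first group and June 2026 for the second, a gap of 4 months. On either series, routine data from districts not yet rolled out could still reach NMED meetings in the first three quarters and, as the checklist is described, would go unscored.

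**Step 3. Why does availability mix with use?** The item is described as recording whether data were used. Suppose, for illustration, that each of k supplying districts has its data referenced at a meeting with the same probability p, independently. Then

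P(item scored yes) = 1 − (1 − p)^k.

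For any fixed p strictly between 0 and 1, this rises as k goes from 3 to 12, although use per district has not changed. If p is 0, or if the item is already yes at the first meeting, it does not rise. So the trend is not forced upward, but a rise cannot be attributed to better use without k and without a microscopy counterpart.

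**Step 4. How many meetings are there?** February 2026 to March 2027 is 14 months; 14 / 3 = 4.7, so about 4 to 5 quarterly meetings. Each one scored without the comparator is a sizeable share of the evidence.

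**The case against.** The strongest reply is that the checklist was never given the comparative task. Its stated purpose is to document how VectorCam data are used, the interviews ask about earlier approaches, the rollout waves are declared not to be comparison groups for causal inference, and the limitations section calls effectiveness descriptive. The form itself is not shown and may hold more than one summary sentence conveys.

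Much of this stands. It limits how far the point reaches, but does not remove it. A descriptive comparison also needs the same indicator under both conditions, and the Aim 3 and sample size sections do speak of a comparison with microscopy and of differences in data usage. The statement that no meaningful control can be constructed sits awkwardly beside a named comparator condition.

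A reader might infer more than the documents support:

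- *VectorCam use must rise, even fourfold (12 / 3).* The described item records whether data were used, not a count of mentions. The two pilot districts started earlier, so a start from zero is not established. Availability is also not use: NMED could ignore the data, and the checklist would show that.
- *Microscopy reporting falls from 12 districts to none.* Nothing says that routine reporting stops in a district when VectorCam starts.
- *The study team itself feeds VectorCam data into the observed meetings.* Data-based decision making is a strategy in the package, and NMED representatives attend the study's own stakeholder meetings. The checklist, however, is used at NMED's routine meetings, and nothing says that the team presents data there.
- *Data use is compared with nothing at all.* The interviews do offer a comparison, though a recalled and perceived one.

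**Conclusion.** The point holds for the observed data-use outcome. As described, the NMED checklist yields no value for the microscopy comparator, and its trend across rollout phases cannot separate wider availability of VectorCam data from greater use of them. The interviews do not fill that gap with observed data.

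The documents do not allow the size of any bias to be calculated, and its direction is not fixed. What can be said is that none of the checklist content described covers routine microscopy data, over about 4 to 5 meetings.

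Two assumptions carry this: that the article's description reflects the form in use, and that routine data can reach the same meetings, which is plausible while districts await rollout. If the form already has an item for routine data, only the description needs correcting. The matter concerns a secondary, descriptive aim. It is a worthwhile and cheap improvement, not a flaw that undermines the study.

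**What to change.** In the description of the NMED meeting checklist under Aim 3, and on the form, score each item at each meeting separately for VectorCam data and for routine microscopy data. Report the two side by side for each meeting, together with the number of districts supplying VectorCam data at that meeting. Recording who introduced the data is optional.

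For meetings already held without the second item, or if it is not added, limit the data-use conclusion to describing uptake of VectorCam data. In that case, reconcile the comparative wording under Aim 3 and the expectation of detectable differences in data usage under Sample Size and Power with Challenges and Limitations.

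Cost: slightly more recording by the same observer at the same meetings, plus a count of supplying districts. The drawback is that earlier meetings may lack the item, so the side-by-side series may begin late.
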